#### Eye Tracking

The eye-tracking component of this study will be conducted using the Tobii Nano Pro (Tobii Tech), a screen-based eye tracker known for its high precision in capturing gaze data. The Tobii Nano Pro offers a sampling rate of 60 hertz, which translates to data collection at intervals of 16.67 milliseconds. This high frequency allows for detailed tracking of eye movements and gaze patterns. To ensure accurate gaze data, a standard 9-point calibration procedure will be performed at the beginning of each session. This process involves directing the participant’s gaze to 9 specific points on the screen to map their eye movements accurately. The calibration will be verified for precision before starting the main trials to ensure reliable spatial and temporal tracking. Participants will be seated approximately 60 cm from the Tobii monitor, which has a resolution of 1600 × 1200 pixels. Participants will be instructed to maintain a still head position and focus attentively on the images displayed on the screen. Participants will view pairs of pictures displayed side by side for 500 or 2000 milliseconds each. Each image pair is matched for shape, color, and background to control for these variables. The following eye-tracking parameters will be measured:

TTFF: time elapsed between the appearance of a picture and the user’s initial gaze fixation within an area of interest. In this case, each product will be defined as a separate area of interest.First fixation duration: time participants gaze at their first fixation point.TFD: length of all fixations within a specific area of interest (in seconds). Average TFD will be used for statistical analyses.Fixation count: number of fixations on stimuli.Eye movement data will be analyzed using Tobi software.

Fixations are defined as periods where the gaze remains stable within a 30-pixel radius for at least 100 milliseconds, and these fixations must be initiated at least 100 milliseconds after picture onset to exclude anticipatory eye movements.

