### Data Collection Plan

#### Dot-Probe Task

The dot-probe task will be implemented using E-Prime 3.0 software (Psychology Software Tools, Inc) for both eye-tracking and ERP components. Each trial will commence with a 500-millisecond presentation of a fixation cross at the center of the screen. This serves to focus participants’ attention on the central point before the food stimuli are displayed. Following the fixation cross, a pair of images (one familiar and one novel) will be shown side-by-side for either 500 or 2000 milliseconds. The side on which each type of image appears is randomized to control for location bias. After the image pair is presented, a dot-probe will appear in the location previously occupied by one of the images. The dot will remain visible for 500 milliseconds. Participants will indicate the location of the dot by pressing the “L” key if the dot appears on the left side of the screen, or the “R” key if it appears on the right side. The response time and accuracy will be recorded for each trial (Figure 1).

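### The 100 ms anticipation rule removes single fixations, not trials, so an early look is erased and the familiar–novel difference in the gaze measures is diluted

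*Protocol article*

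**What the plan says.** All places are in the protocol article.

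- **Eye Tracking, fixation definition:** "Fixations are defined as periods where the gaze remains stable within a 30-pixel radius for at least 100 milliseconds". The anticipation limit is attached to that same definition as a second condition: "these fixations must be initiated at least 100 milliseconds after picture onset to exclude anticipatory eye movements". Both conditions describe a fixation. Neither describes a trial.
- **Eye Tracking, measures:** TTFF runs from picture appearance to the "initial gaze fixation within an area of interest". Each picture has its own TTFF, because "each product will be defined as a separate area of interest". The next measure reads "First fixation duration: time participants gaze at their first fixation point". For TFD the article takes the "length of all fixations within a specific area of interest (in seconds"). A fixation count is listed as well.
- **Dot-Probe Task, start of trial:** "Each trial will commence with a 500-millisecond presentation of a fixation cross at the center of the screen". The stated purpose is to bring attention to the centre. Picture onset is not made to depend on where gaze is. The pair "will be shown side-by-side for either 500 or 2000 milliseconds", with the side of each picture type randomised.
- **Dot-Probe Task, exclusions:** incorrect responses and reaction times below 200 ms or above 1500 ms are removed. These exclusions concern reaction times only.
- **Statistical Analysis:** TTFF and fixation duration are compared between the 500 ms and 2000 ms conditions. The Introduction and Discussion hypothesise a longer TFD for familiar items.

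**The concern.** The rule is meant to remove anticipatory looks. Taken literally, it removes the look and leaves the rest of the trial to be scored as if it had begun at the centre. Three things follow for the picture already under gaze, and for the trial:

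- That picture's TTFF is late if gaze leaves and returns or refixates, and missing otherwise.
- The dwell of the early look drops out of its TFD.
- A later fixation becomes the first fixation of the trial. In the 500 ms condition there may be no countable fixation at all.

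Where gaze rests before the pictures appear cannot depend on which picture will be there. Such trials therefore carry less information on familiar versus novel than trials that start centrally. Averaging them in weakens the contrast that the study sets out to measure.

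**Working it through.** **1. The plan's own figure.** The article gives no figure for this rule. Its one statistical result is the power of 0.820 in Sample Size. With N = 40, f = 0.35, m = 8 and ρ = 0.5, λ = N·f²·m / (1 + (m − 1)ρ) = 40 × 0.1225 × 8 / 4.5 = 8.71. On 1 and 38 degrees of freedom this gives 0.8202, so the figure is reproduced. Nothing below depends on it.

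**2. Timing.** From the article: exposure T is 500 or 2000 ms, a fixation lasts at least 100 ms, and it starts at least 100 ms after onset. If the 100 ms must fit within the exposure (assumed), a countable fixation starts between 100 and T − 100 ms:

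- 500 ms condition: 100 to 400 ms, a window of 300 ms.
- 2000 ms condition: 100 to 1900 ms, a window of 1800 ms.

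Assume an early look starts at s, lasts d, and is followed by a 40 ms saccade. The next fixation starts at s + d + 40. The erased dwell is the part of the look that falls within 0–500 ms.

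| s (ms) | d (ms) | next start (ms) | countable at 500 ms? | erased share of 500 ms |
|---|---|---|---|---|
| −200 | 350 | 190 | yes | 30% |
| −200 | 450 | 290 | yes | 50% |
| 0 | 150 | 190 | yes | 30% |
| 0 | 250 | 290 | yes | 50% |
| 0 | 350 | 390 | yes | 70% |
| 0 | 450 | 490 | no | 90% |
| 99 | 250 | 389 | yes | 50% |
| 99 | 350 | 489 | no | 70% |

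In the 2000 ms condition the next fixation is countable in every row. A look that began 200 ms before onset and lasted only 150 or 250 ms erases 0% or 10%. Its successor (at −10 or 90 ms) is also too early to count.

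**3. Dilution.** Let a be the share of trials with an early look, D the familiar–novel difference in the other trials, and r·D the difference left in the affected trials. Then

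observed difference = (1 − a)·D + a·r·D, so the shrinkage relative to dropping those trials is a·(1 − r).

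- r = 0 (affected trials carry no contrast): 5%, 10% and 20% for a = 5%, 10% and 20%.
- r = 0.5: 2.5%, 5% and 10%.

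**4. Simulation.** The documents give neither a nor r, so gaze sequences were simulated under assumed parameters, comparing the rule as written with dropping the trial.

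- With the next look going to the other picture 30% or 70% of the time, the 500 ms TFD difference shrank by about 3–6%, 8–11% and 17–21% at shares of 5%, 10% and 20%. This is close to r = 0. TTFF at 2000 ms was diluted too.
- With 53% of first looks to familiar, first saccade at about 240 ms, fixations of about 270 ms and that chance varied from 30% to 90%, the shrinkage was 6–10% at a 10% share and 13–20% at 20%.
- With familiar pictures also holding gaze 15 ms longer, one run gave 17.6 against 18.6 ms at a 10% share (1.0/18.6 = 5%) and 15.8 against 17.7 ms at 20% (1.9/17.7 = 11%).

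**5. Scale.** Of 128 trials, a 10% share is 12.8 trials and a 20% share is 25.6.

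**The case against.** The strongest reply is that the article never says an affected trial is kept. That is inferred from silence, and trial validity for gaze data may be settled in a fuller protocol or analysis plan. This stands, and it is why the point is an improvement and not an error. What remains is that the article does state a rule, and that rule acts on the fixation.

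Second, the cross is there to centre attention and side is randomised, so such trials may be few and cannot favour either picture type. Both parts stand. The frequency is unknown and the effect is dilution, not reversal.

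Third, a reader might infer that the next look usually falls on the other picture, so that attention is credited to the wrong one. The documents do not support this. With a 30-pixel radius, a small shift within the same picture already starts a new fixation. A later fixation on the other picture really is on that picture, and its TTFF is correctly timed. The fault lies only in the TTFF and dwell of the picture already viewed, and in which fixation is called first.

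Fourth, a reader might infer that the main harm is a distorted comparison of 500 with 2000 ms. In one simulation, the 2000 ms TFD difference minus the 500 ms difference (rule as written, then trial dropped) was:

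- 5% share: 51.4 − 12.2 = 39.2 against 52.1 − 12.8 = 39.3 ms
- 10% share: 53.7 − 12.7 = 41.0 against 55.0 − 14.1 = 40.9 ms
- 20% share: 51.3 − 10.9 = 40.4 against 53.5 − 13.0 = 40.5 ms

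The contrast moves by 0.1 ms, under 1%. Only at a 30% share does it move visibly (40.2 against 38.4 ms). The values with the trial dropped, which should be constant, scatter from 12.8 to 14.1 and from 51.8 to 55.0 ms, so small shifts in that run should not be read closely. In relative terms, unequal shrinkage at the two durations needs an assumed hold effect.

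**Conclusion.** The point holds as a cheap improvement. The rule removes fixations, and the article pairs it with neither a trial exclusion for the gaze measures nor a requirement that gaze be on the cross at onset. Followed literally, it dilutes the familiar–novel difference in TFD and TTFF roughly in proportion to the share of affected trials. At a 10% share that is about 8–11% of the 500 ms TFD difference, or 5–11% across all the assumptions tried. At a 20% share it is about 11–21%.

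These sizes rest on assumed gaze behaviour and an assumed share, since the documents give neither. The loss of power is small up to a 20% share. The material does not support a bias toward familiar or novel, attention credited to the wrong picture, or a material distortion of the presentation-time contrast.

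**What to change.** In the Eye Tracking section, add a rule at trial level that applies to the eye-tracking measures only: exclude the whole trial when gaze is not within a prespecified central window at picture onset, or when a fixation on either picture starts less than 100 ms after onset. State the size of the window there, before the data are examined, so that it does not become a later choice. Report the share of trials excluded by participant and by presentation time.

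The cost is a sentence or two and a filter. Gaze is recorded throughout (Procedure), onset markers are written to the gaze stream (Software Coordination), and the abstract says analysis has not begun. The downside is that some eye-tracking trials are lost. Reaction-time and electroencephalography data are untouched.

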#### Electroencephalography Acquisition

As an electrophysiological measure of attention, electroencephalography will be recorded during the exposure to food stimulus pictures to determine the P300 and N100 ERPs. Electroencephalography signals will be recorded using the 9-channel B-Alert EEG system, which captures neural signals at a sampling rate of 256 hertz, providing data acquisition approximately every 3.91 milliseconds. This setup ensures the high temporal resolution necessary for detailed analysis of ERPs. Electrodes will be positioned following the international 10-20 system to ensure consistent and reliable data collection. The 9-channel configuration will cover standard locations to accurately capture neural signals. To maintain a clear signal acquisition, the impedance for each electrode will be kept below 5 kΩ, and impedance levels will be checked before data collection begins. An additional 2 electrodes will serve as reference and ground electrodes to improve the accuracy of the recordings. To address ocular artifacts, additional electrodes will be placed at the left and right mastoids, as well as at the supraorbital and suborbital positions of the left eye (for vertical electrooculography, VEOG), and the outer canthi of both eyes (for horizontal electrooculography, HEOG). Then, preprocessing will be performed using the B-Alert software (Advanced Brain Monitoring, Inc) to remove noisy segments of the signal. Subsequently, the signals will be epoch-referenced, with epochs spanning from the onset of the dot presentation to 1000 milliseconds after the presentation of the stimuli. The signal will be filtered at 50 hertz by the device, so there will be no need for additional filtering for power line noise and harmonics. Under appropriate conditions, the amplitude of the P300 indexes response categorization and the depth of encoding of the stimuli; larger amplitude P300s are thought to represent the amount of processing necessary to update neural networks about the changing environment. While there are a number of complementary and competing models of P300 [28], and several identified factors that affect the amplitude and latency of the P300 [31], all agree that stimuli garnering more attentional resources produce larger amplitude P300s. The collected electroencephalography data will be preprocessed using the EEGLAB environment, a tool library for processing electroencephalography data in MATLAB. The adjust plugin in EEGLAB will be used to discard artifacts due to eye movement and muscle activity.

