While some previous studies have suggested a role for visual attentional bias toward familiarity and novelty of stimuli [22], there is a paucity of studies using electroencephalography to examine this, particularly in the context of food choice behavior. Electroencephalography is a noninvasive technique used to measure brain activity in response to stimuli by recording event-related potentials (ERPs). So far, only a few studies have explored integrating electroencephalography, eye-tracking, and dot-probe methods to study attentional bias to food-related stimuli [23]. Of note, no previous study has taken stimulus novelty and familiarity into consideration, nor how the results of this integrated approach associate with the self-report food choices. Familiar stimuli evoke trust and perceived quality from previous positive experiences are suggested to influence an individual’s choices [24]. However, novel products require more cognitive effort to evaluate, leading to longer information processing times [25]. Thus, the main objective of this pilot study is to examine differences in attention to novel compared with familiar food stimuli, using 3 different attention indexes, including electroencephalography, eye tracking, and dot-probe. Indeed, it is hypothesized that participants will exhibit shorter reaction times (RTs) and longer total fixation durations (TFDs) for familiar compared to novel food items, indicating a stronger attentional bias toward familiar foods. In addition, familiar food items will elicit greater P300 amplitudes compared with novel food items, suggesting enhanced attentional engagement and processing.

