#### Intervention

Participants who meet the inclusion criteria will be recruited to complete a dot-probe task while integrated electroencephalography and eye-tracking data are recorded. Each participant will conduct a series of attention-related tasks (an eye-tracking task, a visual probe task, and an ERP task), and, hereafter, a Food Choice Questionnaire (FCQ) to assess food choice. The intervention involves presenting participants with both familiar or novel food items from 4 categories (milk, oil, sauce, and beverages) simultaneously during the dot-probe task to assess attentional biases. In this task, pairs of images (one familiar and one novel food item) will be displayed on a computer screen, followed by a dot-probe appearing in the location of either the familiar or novel item. Participants will be instructed to respond as quickly and accurately as possible by pressing a key corresponding to the location of the dot-probe. Reaction times to the dot-probe will be recorded. Neural responses will be captured using electroencephalography to identify specific brain activity patterns associated with processing the food stimuli, offering insight into the cognitive and neural mechanisms underlying attention. Eye-tracking technology will also be used concurrently to monitor gaze patterns and fixation duration (FD) on each food item, enabling us to quantify the amount of visual attention allocated to familiar versus novel items. No intervention modifications are planned in this study, as they do not apply to the type of intervention used.

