### Statistical Analysis

ERP data will be preprocessed with EEGLAB v14.1.2 toolbox for MATLAB [33], involving noise removal, epoching from stimulus onset to 1000 milliseconds post stimulus, and averaging across epochs to extract ERP components. Potentials reflecting ocular or muscle-related artifacts were removed using logistic infomax independent component analysis [34]. Further artifacts will be removed using the clean_rawdata plugin for EEGLAB.

Regarding dot-probe and electroencephalography attention-related measures (RTs, and N100 and P300 amplitudes, respectively), repeated measures ANOVA will be conducted, including the stimulus type (familiar vs novel across 4 food categories) as a within-subject factor, and group (500 ms vs 2000 ms) as a between-subject factor. Similarly, ANOVA will also be conducted to examine eye-tracking measures (TTFF, FD) between groups (500 ms vs 2000 ms). Post-hoc analyses will be conducted with Bonferroni adjustments for multiple comparisons. In addition, relationships between eye-tracking measures (TTFF, FD) and ERP components (P300 and N100 amplitudes) will be calculated by the Spearman correlation analysis. IBM SPSS Statistics 20 (IBM Corp) software will be used to analyze the data. No interim analyses are scheduled for this study.

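### The two ERP epoch definitions start at different events, and under the picture-locked one the plain averages cannot supply the familiar-versus-novel contrast

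*Protocol article*

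**What the plan says.** All of the following is in the protocol article.

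- **Display.** Dot-Probe Task: "a pair of images (one familiar and one novel) will be shown side-by-side for either 500 or 2000 milliseconds". Intervention says the same: "pairs of images (one familiar and one novel food item) will be displayed on a computer screen". After the pair, "a dot-probe will appear in the location previously occupied by one of the images".
- **Epoch, first statement.** Electroencephalography Acquisition: "epochs spanning from the onset of the dot presentation to 1000 milliseconds after the presentation of the stimuli".
- **Epoch, second statement.** Statistical Analysis: "epoching from stimulus onset to 1000 milliseconds post stimulus", followed by averaging across epochs.
- **Purpose of the recording.** Electroencephalography Acquisition: "electroencephalography will be recorded during the exposure to food stimulus pictures to determine the P300 and N100 ERPs".
- **Model.** N100 and P300 amplitudes go into the same repeated measures ANOVA as reaction time (RT), "including the stimulus type (familiar vs novel across 4 food categories) as a within-subject factor", with presentation time (500 or 2000 ms) as the between-subject factor.
- **Hypothesis.** Introduction: "familiar food items will elicit greater P300 amplitudes compared with novel food items". The Discussion repeats it.
- **Component timing.** Outcome Measures puts the N100 at about 100 ms and the P300 at about 300-600 ms after the stimulus.

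**The concern.** An ERP is defined by the event it is locked to. One section locks it to the dot and the other to a stimulus, which in most of the article means the food picture. Outcome Measures counts time to first fixation from stimulus onset, meaning the picture. The acquisition section distinguishes the dot from the stimuli. The ANOVA factor called stimulus type is the familiarity of the food.

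On that reading a second problem follows. Both kinds of food are on screen in every trial, so a picture-locked epoch belongs to the pair and to neither kind alone. The model nevertheless needs one amplitude for familiar and one for novel.

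The ERP measure is one of the three attention indexes behind the primary outcome, and the same amplitudes feed the Spearman correlations with eye tracking. A null result from the picture-locked average would say nothing about the hypothesis. Two time-locks on the page also leave the choice open until after the data have been seen.

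**Working it through.** **The plan's own figure.** Sample Size reports a power of 0.820. It reproduces as the between-subject test: λ = f²·N·m / (1 + (m − 1)ρ) = 0.1225 × 40 × 8 / 4.5 = 8.71, with 1 and 38 degrees of freedom, giving 0.8202. That is the test of 500 against 2000 ms. It does not bear on whether a familiar-versus-novel ERP contrast exists, so the check below rests on timing.

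**Inputs.** Picture duration is 500 or 2000 ms, with the dot following the pair (Dot-Probe Task). N100 is at about 100 ms and P300 at 300-600 ms (Outcome Measures). I assume no gap between picture offset and dot onset, since none is stated.

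**Step 1: put each reading on one clock, with zero at picture onset (ms).**

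| Reading | 500 ms trials | 2000 ms trials |
|---|---|---|
| Dot onset | 500 | 2000 |
| Analysis section, locked to picture: epoch | 0 to 1000 | 0 to 1000 |
| – P300 window | 300 to 600 | 300 to 600 |
| Locked to dot: epoch | 500 to 1500 | 2000 to 3000 |
| – P300 window | 800 to 1100 | 2300 to 2600 |
| Acquisition section, end counted from picture offset | 500 to 1500 | 2000 to 3000 |
| Acquisition section, end counted from picture onset | 500 to 1000 | 2000 to 1000 (length −1000) |

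The picture-locked and dot-locked P300 windows do not overlap in either duration. They measure different responses.

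**Step 2: look for a familiarity label in a picture-locked epoch.** Each trial gives one waveform, evoked by both pictures. The only familiar-or-novel label that a plain average could use is the item the dot later replaces. Let that label be L and dot onset be d. For any time t before d, if L is balanced against everything already on screen,

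E[Y(t) | L = familiar] − E[Y(t) | L = novel] = 0.

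- N100 at about 100 ms is before d in both durations.
- P300 window, part after the dot = max(0, 600 − d). For d = 500 this is 100 ms of 300. For d = 2000 it is 0.
- That 100 ms holds only the first 100 ms of the response to the dot. The dot's own P300 does not start until 500 + 300 = 800 ms.

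**Step 3: illustration.** A simulation used 40 participants, 128 trials split 64/64 by dot location, and an assumed trial SD of 8 µV, with 2,000 repetitions. Picture-locked amplitudes sorted by later dot location differed by −0.003 µV on average, and a paired test rejected in 4.75% of runs at α = 0.05. With a 1 µV dot-locked difference added, it rejected in 99.5%. The first result follows from the assumption of no difference before the dot, so it illustrates Step 2 and is not separate evidence.

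**Step 4: the dot-locked reading.** Each epoch can be assigned by whether the dot replaced the familiar or the novel item, the natural sorting for RT. The contrast then exists, but the evoking event is a dot at a location, not a food picture.

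**The case against.** The best defence is that both sections mean the dot. The text under Figure 1 calls the dot the target stimulus and the pictures the cue, and RT and ERP share one ANOVA. Counted from picture offset, the acquisition wording gives an ordinary 1000 ms dot-locked epoch in both durations. This stands as a possible reading, so a reader should not infer from the negative-length window that the acquisition rule is impossible; that holds on only one reading of its end point. The defence does not remove the point, because the hypothesis and the stated purpose of the recording both speak of responses to food pictures.

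A reader might also infer that the ERP contrast is exactly zero, with power equal to α whatever the truth. The documents do not support that. It holds only for picture-locked, non-lateralised averages sorted by a dot location balanced against familiarity, and the article never states that procedure. Comparing electrodes contralateral and ipsilateral to the familiar picture, or locking to fixations with the synchronised data described in Software Coordination, could recover a picture-related contrast. Neither is described; Statistical Analysis speaks only of averaging across epochs.

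It is fair that a condensed article may leave the rule assigning epochs to cells to a fuller plan. Two conflicting start events within the article are not an omission of that kind. The Abstract and the text under Figure 1 describe the pairings more loosely, but Intervention and Dot-Probe Task fix mixed pairs. Finally, nothing says a null would be reported as absence of neural bias; that is a risk, not a stated intention.

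**Conclusion.** The point holds in a limited form. The two sections give conflicting time-locks, 500 or 2000 ms apart, unless the analysis section uses stimulus for the dot. On its natural, picture-locked reading, the plain averaged N100 and P300 cannot supply the familiar-versus-novel factor or test the stated P300 hypothesis. The sole exception is a possible trace of the dot response in the last 100 of 300 ms of the P300 window in 500 ms trials. On the dot-locked reading the contrast is sound but answers a different question from the one the hypothesis asks.

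This rests on mixed pairs in every trial, no gap before the dot, plain averaging, and dot location balanced against familiarity. The article says that all dot locations are tested but does not expressly state that balance. The conclusion does not depend on sample size. It should be settled before any ERP averages are computed.

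**What to change.** - **One time-lock in both sections:** from dot onset to 1000 ms after dot onset.
- **A stated assignment rule:** each epoch is familiar or novel according to which item the dot replaced, as for RT.
- **A matching hypothesis:** state the N100 and P300 predictions as differences in the response evoked by the probe.
- **Picture-locked averages:** report plain ones only at pair level.
- **Comparison of durations:** make it on the familiar-minus-novel difference. Say that overlapping picture-evoked activity cancels there only if the overlap is additive and dot location is balanced against familiarity within each cell.

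The cost is wording plus recutting of epochs. E-Prime marks the beginning and end of each stimulus presentation (Software Coordination), and the Abstract says analysis had not begun at submission, so no new data should be needed. The real price is interpretive: the ERP then indexes attention to the probed location, not direct processing of each picture, and the claims must say so. If the investigators want a picture-evoked contrast, they should instead specify a side-sensitive (contralateral versus ipsilateral) or fixation-locked analysis in place of the plain average.
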